**Exclusion criteria**
Meditation or meditative movement practice (ie, yoga, tai chi, and qi gong) of ≥60 minutes per month in the past 6 monthsUse of any consumer-based meditation appResiding outside of the United StatesAny planned change in pharmacological therapy (ie, new drug) during the study time frame (ie, 20 weeks)Self-reporting sleep-disordered breathing or sleep movement disorderTaking sleep medications or supplements ≥3 times per weekSelf-reporting any other diagnosed and uncontrolled medical or psychiatric condition

### Intervention Group (Calm)

Calm does not provide its users with a specific prescription for how often to use the app (frequency) or how long to use the app (dose); users self-select the frequency, dose, and timing of engagement, as well as which content and features to use. The Calm intervention participants will be asked to complete a minimum of 10 minutes per day of meditation via Calm, at any time of day for 8 weeks. During weeks 1 to 4, participants will be asked to complete the introductory 30-day program *How to Meditate* comprising 30 days of 10-minute daily meditation along with education about what mindfulness is, how to practice and achieve it with meditation, the seated or reclining positions to use for meditation, and how to monitor and guide their breathing. During weeks 5 to 8, participants will be asked to complete one daily meditation that may include the *Daily Calm*, a different 10-minute mindfulness meditation each day, or a meditation from various series of meditations (eg, loving-kindness and 7 days of managing stress). Participants will have complete autonomy over choosing the meditation, which includes options for at least 10 minutes (meditation periods are tracked). After completing their daily meditation, participants will also be able to use the app content more broadly (ie, nonmeditative content, including Sleep Stories and Daily Move) based on their preference.

Calm meditation focuses on mindfulness components [66], breathing techniques, and body scans, all of which are consistent with core mindfulness practices, such as MBSR (nonjudgmental moment-to-moment awareness) [67] and one of Vipassana’s principles—objective observation of physical sensations in the body [68]. As an ideal dose for mindfulness meditation interventions has not been established because of considerable variability in intervention prescription [69], the 10-minute daily dose was chosen, as Calm currently offers 10-minute meditations (daily and series meditations), which corresponds to how long users typically meditate using the app. Practical guides recommend that beginners start with short daily meditations lasting between 10 and 30 minutes per session [26,70]; thus, the intervention prescription will be a minimum of 10 minutes per day of meditation to be effective but not overly burdensome.

Participants will be allowed to choose the time of day when they meditate. Giving participants autonomy over choosing the time of day for meditation mirrors the way in which Calm’s paying subscribers use the app, thus yielding benefits (eg, ecological validity and participant satisfaction) that likely outweigh those of imposing strict controls over the timing of use, which could lead to lower adherence (eg, missed or truncated practice). Participation (meditations completed, time of day, length of time, and nonmeditative content used) will be tracked using the Calm app throughout the study and addressed in sensitivity analyses.

After completion of the 8-week study intervention period, the Calm intervention participants will no longer have to complete daily meditations but will continue to have access to the app for 12 additional weeks during the follow-up period. Participation in the Calm app will continue to be tracked during this time.

### Control Group (Health Education Podcast)

Similar to the Calm intervention group, podcast group participants will listen to a minimum of 10 minutes per day of a health education podcast delivered via a mobile app for 8 weeks (Tables 1 and 2). A library of health education podcasts will be available on the app, with carefully chosen content that excludes any recommendations for sleep, meditation, or mindfulness-like principles or practice. Participants will be able to select the podcast based on title, time, or both in an effort to mirror the delivery of meditations in the Calm intervention group. Podcast group participants will also be encouraged to use other components of the podcast. Participation (podcasts completed, time of day, length of time, and components used) will be tracked on the app throughout the study period. After completion of the 8-week sham intervention period, the podcast group participants will no longer be asked to listen to daily podcasts but will continue to have access to the app for 12 additional weeks during the follow-up period. Participation in the podcast app will still be tracked during this period. Upon completion of the entire 20-week study period, podcast group participants will be given a discount code for 6 months of free access to the Calm app.

**Table 1 table1:** Calm and podcast group prescriptions.

Week	Calm intervention group	Podcast group^a^
Week 1: total 7 days	Daily introductory 10-minute meditation	Daily 10-minute health education podcasts
Weeks 2-4: total 21 days	Daily 10-minute exploration of mindfulness meditation	Daily 10-minute health education podcasts
Weeks 5-20: Full access	Full library of individual and series of 10-minute meditations	Full library of podcasts available

^a^Podcasts will be uploaded weekly, except during weeks 5-20 when the remaining full library will be uploaded.

**Table 2 table2:** Examples of Calm and podcast group prescriptions.

Group and examples			Minutes
**Ca** **lm intervention group**			
	Returning to the Here and Now	10	
	Acceptance	11	
	Paying Attention	10	
**Podcast group**			
	Alcohol and Cancer	10	
	Community Gardening	10	
	10 Ways to Have a Better Conversation	12	

### Retention and Adherence Strategies

We will use self-determination theory (SDT) and SDT-based strategies to guide our protocol and promote adherence [71]. The SDT postulates that the initiation and maintenance of behavior is influenced by three basic needs:(1) competence, or the need to produce desired outcomes and to experience mastery; (2) autonomy, or the need to feel ownership of one’s behavior; and (3) relatedness, or the need to feel connected to others [72]. Participants will be encouraged to use the features built into the Calm intervention or podcast, which are designed to help maintain engagement and adherence in their assigned app. All these features are consistent with practices that help individuals participate in health behaviors [71], and these features are identical in both apps. To promote autonomy, a feature of the Calm and podcast apps includes time spent meditating or listening to podcasts—participants can go to their Calm profile and they are automatically provided the total time they have spent meditating or listening (time from the first meditation or podcast to present), total sessions, and longest streak after each use. To promote competence, the Calm and podcast apps include a reminder that participants can set in the app that will send them a push notification to meditate or listen to a podcast at a set time each day. To promote relatedness, the final feature of the Calm and podcast apps includes *Share Your Stats*, which allows participants to share summaries of their meditation or podcast listening use with others via SMS text messages, emails, or social media (eg, Facebook, Pinterest, or Instagram).

In addition to the above app features, EZTexting (a commercial SMS text messaging–based platform) will be used to send a brief, automated phone call, email, or SMS text message (based on participant preference) at the beginning of the week to encourage continued participation, with the message and conversation grounded in the 3 tenets of SDT (ie, autonomy, competence, and relatedness). Participants who are not meditating or listening to the podcast episodes for at least 10 minutes per day or 70 minutes per week for >3 consecutive days will receive a midweek phone call, email, or text (based on participant preference) through EZTexting. Participants could opt out of these follow-up messages at any time during the intervention. Research staff will track adherence information throughout the study and determine whether the patterns of use are similar across arms. Furthermore, both the Calm intervention and podcast will automatically show the user their time spent in meditation or listening for the day, the total time since the start of the study, and the longest streak as a reinforcing self-management technique. Finally, the Calm intervention and podcast also include reminder tools in which participants can set reminders on their phones to participate [73]. All study participants will receive a monetary incentive for completion of the baseline (US $15), postintervention (US $25), and follow-up (US $35) assessments, including blood draws, for a total incentive opportunity of US $75 paid in one lump sum at the end of the study if all 3 outcome time points are completed.

### Study Outcomes and Measures

#### Overview

Table 3 presents the study outcomes and measures. All study participants will be asked to complete web-based questionnaires via REDCap at 3 time points: baseline (week 0), postintervention (week 8), and follow-up (week 20). In addition, participants will complete a weekly web-based sleep diary via REDCap from weeks 1 to 8 and at the end of week 20. Participants will also complete a weekly log via REDCap regarding their satisfaction with the study and whether there have been any changes in their cancer therapy, sleep medication and supplement use, and disease status. The weekly satisfaction logs will specifically include questions to assess the participants’ overall perceptions of their meditation or podcast sessions. If the participant meditates or listens to a podcast, they will be asked about their likes, dislikes, facilitators, and barriers. If they do not meditate or listen to a podcast, they will be asked what would help them.

**Table 3 table3:** Summary of data collection.

Data, outcomes, and measures				Week 1		Weekly		Week 8		Week 20
**Aim 1**										
	**Sleep disturbance (subjective)**									
		Insomnia Severity Index	✓				✓		✓	
		PROMIS^a^ Sleep Disturbance	✓				✓		✓	
		PROMIS Sleep-Related Impairment	✓				✓		✓	
		Sleep diary			✓				✓	
	**Sleep disturbance (objective)**									
		Actiwatch			✓^b^				✓	
**Aim 2**										
	**Inflammation**									
		Serum cytokines and proteins (TNF-α^c^, interleukin-6, interleukin-8, and CRP^d^)	✓				✓		✓	
	**Fatigue**									
		PROMIS Adult Cancer Fatigue	✓				✓		✓	
	**Depression**									
		PROMIS Depression	✓				✓		✓	
	**Anxiety**									
		PROMIS Anxiety	✓				✓		✓	
**Demographics**										
	**Biological sex**									
		Self-report	✓							
	**Age**									
		Self-report	✓							
	**Race and ethnicity**									
		Self-report	✓							
	**Income**									
		Self-report	✓							
	**Education**									
		Self-report	✓							
	**Marital status**									
		Self-report	✓							
	**Occupation**									
		Self-report	✓							
**Disease and treatment variables**										
	**Comorbidity condition**									
		Charlson Comorbidity Index	✓							
	**Blood counts**									
		Complete blood count	✓				✓		✓	
	**Sleep medications**									
		Self-reported			✓				✓	
	**Cancer therapy changes**									
		Self-reported			✓				✓	
	**BMI**									
		Self-reported height and weight	✓							
**Fidelity and process**										
	**Meditation participation**									
		Self-report log			✓					
		Calm-provided data			✓					
	**Podcast participation**									
		Self-report log			✓					
		App-provided data			✓					
	**Satisfaction**									
		Self-report log			✓					
	**Check-ins and reminders**									
		Email, SMS text message, and phone call			✓					

^a^PROMIS: Patient-Reported Outcomes Measurement Information System.

^b^Assessed daily during the intervention period (weeks 0-8) and for a 7-day period at week 20.

^c^TNF-α: tumor necrosis factor-α.

^d^CRP: C-reactive protein.

#### Demographics

Demographic characteristics will be self-reported at baseline and will include biological sex, age, race, ethnicity, marital status, income, education, and occupation.

#### Clinical Data

Clinical characteristics will include a comprehensive assessment of cancer-specific disease information (eg, comorbidities and complete blood count); other comorbidities (Charlson Comorbidity Index) [74]; self-reported weight and height; and current pharmacological treatment information, including sleep medication.

#### Primary Outcomes (Sleep)

The primary outcome of changes in sleep disturbance will be assessed using the Insomnia Severity Index (ISI). The ISI, a 7-item measure of reported insomnia symptom severity over the past 2 weeks, has been validated among patients with cancer (Cronbach α=.90) [75]. Total scores range from 0 to 28, with scores of 8 to 14 and ≥15 indicating subclinical and moderate to severe insomnia symptom severity, respectively [75]. An ISI change score >7 is considered a clinically meaningful response to treatment [75]. Sleep will secondarily be assessed using the National Institutes of Health (NIH) Patient-Reported Outcomes Measurement Information System (PROMIS) Sleep Disturbance Short Form 8b, PROMIS Sleep Impairment Scale, actigraphy, and sleep diaries. The PROMIS Sleep Disturbance Short Form 8b comprises 8 items assessing various aspects of sleep on a 1 to 5 Likert scale. The measure generates a total summed score, which is then converted to a standardized *t* score for analysis [76]. The NIH PROMIS Sleep Disturbance Short Form 8b is a reliable and valid measure for assessing sleep disturbance in patients with cancer (Cronbach α=.86) [76]. The PROMIS Sleep-Related Impairment Short Form 8a comprises 8 items assessing various aspects of sleep-related impairment (self-reported perceptions of alertness, sleepiness, and tiredness during usual waking hours and perceived functional impairments during wakefulness associated with sleep problems or impaired alertness) on a 1 to 5 Likert scale. The measure generates a total summed score, which is then converted to a standardized *t* score for use in analyses [77,78]. The PROMIS Sleep-Related Impairment Short Form 8a is a reliable and valid measure for assessing impairments associated with sleep across a range of healthy and patient populations reporting sleep disturbance and sleep impairments (Cronbach α=.85-.91) [77,78].

Sleep will also be assessed objectively via wrist-worn actigraph, specifically, via an Actiwatch Spectrum Plus device (Philips Respironics, Inc). Participants will wear the Actiwatch daily throughout the 8-week intervention period, mail it back to research personnel after week 8 (the Actiwatch has a maximum battery life of 68 days), and receive an Actiwatch to wear again for a 7-day period during the follow-up period or week 20. The Actiwatch Spectrum Plus is a valid, reliable, and objective assessment of sleep to be worn on the nondominant wrist 24 hours a day and 7 days a week. This assesses the motion and ambient light data used to analyze the sleep and circadian rhythm parameters. Actigraphy data of ≥5 nocturnal periods recorded per week during the intervention period (ie, week 0-8) and during the 7-day follow-up or week 20 will be considered valid, and the actigraphy data will be binned weekly. The sleep-wake status in each 30-second epoch during the rest intervals will be determined with the Actiware version 6.1.2 (Phillips) scoring algorithm at the medium wake sensitivity threshold. The Actiware software contains automatic off-wrist detection and scoring. All main and minor rest intervals will be verified, with participants entering the rest interval onset and offset times, which are marked at the epoch level when the participant pushes a corresponding button on the device. If these event markers are absent, then the rest intervals will be verified using a daily sleep diary.

Finally, sleep will be further assessed using the Consensus Sleep Diary (CSD). The CSD will be used to assess reported bedtimes and wake times to determine the sleep and wake windows of the main and minor sleep periods [79]. Similar to the actigraphy data, sleep data from the CSD will also be binned weekly. The following night-level and averaged sleep metrics will be derived from both sleep diaries and actigraphy: bedtime, wake time, time in bed, total sleep time, sleep onset latency, wakefulness after sleep onset, number of awakenings, and sleep efficiency ([total sleep time/time in bed]×100%). Sleep efficiency from both sleep diaries and actigraphy will be the main secondary sleep outcome of interest.

#### Secondary Outcomes

Inflammatory biomarkers with serum cytokines and proteins (TNF-α, IL-6, IL-8, and CRP) will be objectively assessed from participant blood samples. The participants’ blood draw instructions will include the address of the nearest Quest Diagnostics Patient Service Center (there are approximately 2200 centers located across the United States). Participants will be instructed to have their blood *drawn in the morning before 10 AM* within 2 weeks of notifying research personnel that they received their package and to repeat their blood draw at postintervention (8 weeks) and follow-up (20 weeks) time points. Participants will not need to fast and follow any other *day-of* procedures. In our prior work, we had high compliance with this method (92.6% at baseline and 70.4% at the postintervention time point) despite offering no incentives for completion of the blood draws [80]. A certified phlebotomist will perform all blood tests, drawing 3 mL of blood. Blood will be transferred into a plastic screw-cap vial and stored on cold packs. The Patient Service Center will mail the drawn blood to the Clinical Laboratory Improvement Amendments–-certified laboratory at the Quest Diagnostics Nichols Institute (San Juan Capistrano, California) for analysis. There will be no cost to the participants. Quest Diagnostics will provide test results to research staff via a secure web-based platform.

Fatigue and emotional distress (ie, anxiety and depression) will be assessed using the NIH PROMIS Adult Cancer Fatigue 7a (7 items), NIH PROMIS Emotional Distress-Anxiety Short Form 7a (7 items), and NIH PROMIS Emotional Distress-Depression Short Form 8a (8 items). Each of these measures asks participants questions on a 1 to 5 Likert scale and generates a total summed score, which is then converted to a standardized *t* score for use in the analyses. These NIH PROMIS instruments are reliable and valid measures of fatigue (Cronbach α>.86), anxiety (Cronbach α=.90), and depression (Cronbach α=.91) in patients with cancer [76].

### Statistical Analysis

#### Sample Size and Power

All estimates presented here are conservatively based on a generalized linear mixed model analytic approach, in which the focal effect is an arm (Calm vs podcast) × time (baseline vs 8 or 20 weeks) interaction. A generalized linear mixed model approach affords lower power than the preferred analysis of covariance (ANCOVA) approach, which will be pursued if the model’s homogeneity of effect assumption is met (see the *Analytic Approach* section). Assuming a sample SD for ISI scores of 6.0 (derived from the literature on sleep disturbance among patients with cancer [81-85]) and Cronbach α=.05, a complete-case sample size of 28 (n=14 pee arm) would afford a power of 0.80 to detect a clinically meaningful between-arm (Calm vs podcast) differences in ISI scores of >7 points (ie, a standardized between-arm difference of Cohen *d*=1.33). However, anticipated effects on other sleep measures and measures of well-being are generally much more modest; accordingly, the study sample size was determined based on anticipated intervention effects on these outcomes rather than those on the ISI. In our previous work, we found moderate effects of meditation on self-reported psychological well-being (aim 2; Cohen *d*_s_=0.31-0.44), self-reported sleep disturbance assessed via the PROMIS Sleep Disturbance questionnaire (Cohen *d*=0.47), and inflammation biomarkers (Cohen *d*_s_=0.41-0.50) [39]. The meta-analysis by Duong et al [86] suggests somewhat stronger effects of mindfulness (standardized mean difference 0.50) and relaxation (standardized mean difference 0.94) interventions on fatigue. Assuming an effect size typical of those observed across these various outcomes (Cohen *d*=0.45), a conservative estimate of the pre-post correlation for outcome scores (*r*=0.30) and Cronbach α=0.05, a complete-case sample (at 8 weeks) of 220 (n=110 per arm) should afford a power of 0.80 to detect significant between-arm differences in secondary outcomes (and power >0.99 to detect a clinically meaningful difference in ISI scores). Anticipating up to 20% attrition at 8 weeks, we will enroll and randomize 276 participants (n=138 per arm). For aim 3, anticipating up to 30% attrition by week 20 (yielding 194 complete cases; n=97 per arm), tests of intervention effects should have power=0.80 to detect the effects of Cohen *d*≥0.48. Multivariable linear regression analyses of potential dose-response effects on outcomes will take two forms: (1) analysis of all available cases with a dose coded as 0 for the podcast group and (2) analysis using data from the Calm group only. These analyses should have a power of 0.80 to detect small (*r^2^*≥0.039) and moderate (*r^2^*≥0.076) linear dose-response effects.

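### The ISI change of >7 points is given as a response to treatment but is used as the difference between arm means, so the stated power of >0.99 for the primary outcome refers to a misapplied target

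*Protocol article*

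**What the plan says.** Only the protocol article is at hand. Under Primary Outcomes (Sleep) it names the ISI, a 7-item score from 0 to 28, as the primary measure and adds: "An ISI change score >7 is considered a clinically meaningful response to treatment".

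Sample Size and Power uses a model in which "the focal effect is an arm (Calm vs podcast) × time (baseline vs 8 or 20 weeks) interaction". The ISI calculation begins "Assuming a sample SD for ISI scores of 6.0" and states that 28 complete cases, 14 per arm, "would afford a power of 0.80 to detect a clinically meaningful between-arm (Calm vs podcast) differences in ISI scores of >7 points", glossed as "ie, a standardized between-arm difference of Cohen *d*=1.33".

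The section then says that the sample size was set on other outcomes, not on the ISI. It takes d=0.45, a pre-post correlation of 0.30 and 110 complete cases per arm at week 8 for power 0.80, "and power >0.99 to detect a clinically meaningful difference in ISI scores". With up to 20% attrition this leads to 276 randomized. Among the team's earlier results it cites d=0.47 for sleep disturbance on the PROMIS questionnaire. It cites no earlier effect on the ISI.

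**The concern.** A patient's change from baseline and a difference between two arm means are different quantities. A threshold for the first says how much one person must improve to count as a responder. It does not say how far apart the arm means must be. When the control arm also improves, or when only some patients respond, a treatment can produce worthwhile extra responders with a mean difference well below 7. The article gives no basis for a between-arm threshold of that size.

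Two things are at stake. First, >0.99 is the only power given for the primary outcome at the real sample size, and it describes an effect far larger than any that the article cites for sleep disturbance. A reader learns nothing from it about power at a plausible ISI difference. Second, having called >7 points between arms clinically meaningful, the article leaves a significant result of 2 or 3 points awkward to interpret: by its own wording such a result falls short, although the threshold was never meant for means.

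**Working it through.** **Inputs, all from Sample Size and Power:** SD 6.0; r=0.30 (stated for the 110-per-arm calculation and applied here to the ISI as well); type I error 0.05 (printed as Cronbach α, read as the significance level; taken as two-sided, which reproduces the figures); arm × time model; 110 complete cases per arm; d=0.45 and d=0.47.

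**1. The plan's own figures.** Arm × time with two time points is a comparison of change scores.
- SD of change = 6.0 × √(2 × (1 − 0.30)) = 6.0 × 1.183 = 7.10.
- The ISI total is a whole number, so the first value above 7 is 8, and 8/6.0 = 1.33, the stated d.
- Noncentral t, 8 points: power is 0.79 at 13 per arm and 0.82 at 14. The stated 14 is right.
- Same method at d=0.45: 109.5, so 110 per arm, power 0.80. Right.
- At 110 per arm the standard error is 7.10 × √(2/110) = 0.957. Then 8/0.957 = 8.4 and 7/0.957 = 7.3 standard errors, so power is above 0.9999 for either. The stated >0.99 is numerically right.

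**2. How the target compares with the cited effects.**
- 1.33/0.47 = 2.8.
- If d=0.45 to 0.47 carried over to the ISI, it would be 0.45 × 6.0 = 2.7 to 0.47 × 6.0 = 2.8 points. This is an assumption, because those effects come from other measures.

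**3. What 110 per arm can do on the ISI.** For ANCOVA the residual SD is 6.0 × √(1 − 0.30²) = 6.0 × 0.954 = 5.72. All figures are at two-sided 0.05, before any Hommel adjustment.

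| | Arm × time (SD 7.10) | ANCOVA (SD 5.72) |
|---|---|---|
| Difference with power 0.80 | 2.69 points (d=0.449) | 2.17 points (d=0.362) |
| Power at d=0.45 (2.7 points) | 0.80 | 0.94 |
| Power at d=0.47 (2.8 points) | 0.83 | 0.95 |
| Smallest significant observed difference | 1.97 × 7.10 × √(2/110) = 1.9 points | 1.97 × 5.72 × √(2/110) = 1.5 points |

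Under arm × time, power of 0.99 needs about 4.1 points (d about 0.69).

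**4. Effect of multiplicity.** The Analytic Approach section says that Hommel-adjusted P values will be used. If the ISI were one of, say, five tests (an illustrative number), the strictest level would be 0.05/5 = 0.01. Power at d=0.47 would then be 0.64 (arm × time) or 0.85 (ANCOVA). This is a lower bound for that illustration, not a forecast.

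**The case against.** The strongest defence is that every printed number is correct and that nothing in the design rests on the ISI calculation. Both parts stand. The article writes >7 and d=1.33, which is 8 points on a whole-number scale, and 14 per arm follows. The article also says plainly that N was set on the other outcomes at d=0.45, so a similar effect on the ISI would still have power of about 0.80 or more before adjustment. It attaches >0.99 only to the difference that it calls clinically meaningful, so power of 0.83 at d=0.47 does not contradict it.

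A reader might infer three stronger things that the document does not support:
- *That n=14 is an arithmetic error.* At exactly 7 points, d is 1.17 and 18 per arm are needed (14 give power 0.71). But the text does not power for exactly 7.
- *That the team's own data show that 8 points will not occur.* The d=0.47 is from PROMIS, and no ISI effect is reported. The comparison is suggestive, not proof.
- *That the lack of a responder analysis is a fault.* A journal article may leave that to a full protocol or SAP, which is not shown.

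The defence does not reach the central point. A criterion introduced as response to treatment is reused, with no justification, as a between-arm difference, and the primary outcome's only power figure at the actual N hangs on it.

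**Conclusion.** The point holds as a misapplied threshold, not as a calculation error. The article's >7 is a within-patient response criterion in one section and a difference between arm means in another. The resulting power of >0.99 is correct for 8 points but uninformative, because that target is about 2.8 times the nearest effect cited. A more useful description is 0.80 power for about 2.7 ISI points (arm × time) or 2.2 points (ANCOVA). If the effect is assumed to be d=0.45 to 0.47, power is 0.80 to 0.83 or 0.94 to 0.95. These figures assume SD 6.0, r=0.30, 110 complete cases per arm and two-sided 0.05 without Hommel adjustment; if the ISI is in the adjusted family they are upper limits. The sample size, the analysis and the conduct of the trial are unaffected. What changes is the claim made for the primary outcome and the way a significant result may be described.

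**What to change.** - In Sample Size and Power, state that an ISI change of >7 is a within-patient response criterion and not a between-arm difference.
- Replace the statements on d=1.33, 14 per arm and >0.99 with the detectable difference: with 110 complete cases per arm, SD 6.0, r=0.30 and two-sided 0.05, power is 0.80 for a mean ISI difference of about 2.7 points (arm × time) or 2.2 points (ANCOVA). Add the power at d=0.45 to 0.47, labelled as an assumption carried over from other measures. Say that all of this is before any Hommel adjustment.
- Do not use the 7-point threshold to describe a significant mean difference as clinically meaningful.
- Optional and supportive: report by arm the proportion whose ISI falls by more than 7 at week 8. Entry is by PSQI >5 with no ISI floor, so also give the number with baseline ISI of 7 or less, who cannot meet the criterion.

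The cost is a few sentences and, if the option is taken, one extra summary of data already collected. N=276 stays. The downside is a less favourable stated power for the primary outcome.
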